### Exploratory outcome measures

#### The Maternal Antenatal Attachment Scale

The Maternal Antenatal Attachment Scale (MAAS) is a widely used measure of the maternal-fetal bond [50]. The maternal-fetal bond has been defined as “the emotional tie or bond which normally develops between the pregnant woman and her unborn child” [51]. The theoretical basis of MAAS is a hierarchical model of adult attachment [50]. Within this model, the core experience of maternal attachment is the mothers love for her unborn child. The MAAS consists of 19 items covering two subscales: 1) Quality of attachment (11 items) and time spent in attachment mode (8 items) [52]. All items are rated on a five-point scale. The minimum score for the total MAAS is 19 and the maximum is 95. The scores for the subscales range between 11 and 50 (Quality of attachment) and between 8 and 40 (Time spent in attachment mode). Higher scores reflect, respectively, a positive quality of attachment and a high intensity of preoccupation with the fetus [52]. Moreover, MAAS scores can be divided into four maternal attachment styles based on mean scores on the two subscales [53]. The MAAS has demonstrated good psychometric properties in terms of structural validity and internal consistency [54].

#### The Childbirth Experience Questionnaire

The Childbirth Experience Questionnaire (CEQ) assess different aspects of childbirth experience [55]. The CEQ contains 22 statements assessing four domains of the childbirth experience; own capacity, professional support, participation, and perceived safety. For 19 of the items the response format is a 4-point Likert Scale whereas the last three items use a visual analogue scale (VAS). Higher scores reflect a more positive birth experience. The CEQ has demonstrated an acceptable construct validity and reliability in a Danish setting [38].

### Mediator variables

#### The Five-Facet Mindfulness Questionnaire

The Five-Facet Mindfulness Questionnaire (FFMQ) assesses five general facets of being mindful in daily life: observing, describing, acting with awareness, non-reactivity to inner experience, and non-judging of inner experience. Items are rated on a five-point Likert scale ranging from 1 “never or very rarely true” to 5 “very often or always true”. Higher scores suggest higher levels of mindfulness. Previous studies have provided good support for the construct validity of the FFMQ [56].

#### The Self-Compassion Scale

The Self-Compassion Scale (SCS) measures the ability to have a healthy stand towards oneself that does not involve evaluations of self-worth [57]. The scale consists of 12 items and responses are given on a 5-point scale from ranging from 1 “almost never” to 5 “almost always”. Higher scores indicate more self-compassionate behavior. The psychometric properties of the scale has been extensively evaluated [57].

#### Participant characteristics

Baseline data on estimated due date, age, marital status, number of children, social support, working status, education, obstetric complications (e.g. gestational diabetes), current use of psychotropic medication, therapy and experience with mindfulness-based interventions will be collected by means of a self-report questionnaire. Data on history of mental disorders and psychosocial vulnerabilities, and data on time and mode of delivery, birth length and weight will be collected from the participants’ medical record.

### Sample size

The primary outcome is change in mental well-being (WHO-5) from baseline to post-intervention. The aim is to include 240 psychosocially vulnerable pregnant women in the period from March 2022 and until the desired number has been reached. About 750 women are referred to the obstetric ambulatory clinic every year and the time span is therefore considered realistic. Out of 240 pregnant women, 168 (70%) is expected to complete the study based on the dropout rate in the feasibility trial [41]. With this sample size, a standard deviation of 15.6 (data from the feasibility trial) and a two-sided alpha of 5%, the study has 82% power to detect a difference of 7 on the WHO-5 between the two study groups, and 91% power to detect a difference of 8 on the WHO-5.

### Randomization

The study will use the REDCap randomization module hosted by Aarhus University for the randomization procedure. To secure concealment, a data manager from Aarhus University, not otherwise involved in the study, programed the randomization algorithm. Enrollment and randomization is conducted by the responsible researcher, and takes place after the statement of consent has been signed and the first questionnaire has been filled in. Participants are randomized in a 1:1 ratio. Inclusion and thus randomization will take place consecutively.

### Criteria for discontinuing allocated interventions

Criteria for discontinuation of study participation is if requested by the participant.

### Statistical analysis plan

Statistical analyses will be performed using SPSS for Windows (version 28; IBM Corp, Armonk, NY) or Stata (version 16). Recruitment, participation and retention rates will be reported in a CONSORT flow diagram [58]. Analyses on the primary outcome will be conducted on the intent-to-treat population meaning all randomized participants with completed baseline assessments. Compliance is considered as participation in five or more of intervention-scheduled classes.

Baseline sociodemographic data will be presented by means of frequencies (percentages), medians (interquartile range), and means (SD), according to their level of measurement and statistical distribution.

Statistical analysis of primary outcome, mental wellbeing, will be performed using a repeated measurement model with systematic effects, randomization arm, time (baseline, 3, 6 and 9 months post-randomization), intervention (prenatal MBSR, waitlist control group), interaction between time and intervention, baseline values of: age, perceived stress and use of psychotropic drugs. The model will include random effects of person and “scheduled group”. The primary effect estimate is the mean difference in change since baseline between the intervention group and the control group at nine months post-randomization. The change from baseline at 3 and 6 months will also be reported. Equivalent models will analyze secondary outcomes, stress, anxiety and depression. The change from baseline to three months after randomization in maternal antenatal attachment will be analyzed in a model with the systematic effect of intervention, baseline mental wellbeing, perceived stress, age, number of children and random effect of “scheduled group”. Equivalent models will be used in the analysis of experience of childbirth. A per-protocol analysis of the primary outcome will be performed with three intervention levels: (1) attending five or more of intervention-scheduled sessions, (2) attending less than five of intervention scheduled sessions and (3) waitlist control group. No subgroup analyses is planned. Standard errors will be based on the bootstrap method, resampling persons.

The five measurement points allow to test whether changes in the proposed mediators, i.e. mindfulness and self-compassion, are associated with changes in the proposed outcomes. Structural equation modelling will be used for the statistical analyses of the proposed mechanisms [59].

Four sensitivity analyses is planned to evaluate the size of bias if data not being missing at random. In each of the four analyses, missing outcomes after baseline will be imputed as the model based estimated value when using the observed data, plus a systematic deviation. First, the deviation will be zero in the waitlist control group and + 0.2*SD in the prenatal MSBR group. Second, the deviation will be zero in the waitlist control group and − 0.2*SD in the prenatal MSBR group, and then + 0.2*SD in the waitlist control group and zero in the prenatal MSBR group in the third analysis. In the fourth and final analysis, the deviation will be -0.2*SD in the waitlist control group and zero in the prenatal MSBR group.

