### Design

This protocol adheres to the guidance of the Standard Protocol Items: Recommendations for Interventional Trials (SPIRIT) statement for reporting randomized clinical trials [42]. The design is a single-center, parallel group, randomized controlled trial comparing prenatal MBSR as add on to usual care (UC) with usual care alone. Participants are randomized in a 1:1 ratio to an intervention group or a waitlist control group receiving care as usual. Participants in the waitlist control group are offered participation in an equivalent MBSR program for mother and baby after the follow-up period. An outline of the study timeline is shown in Table 1.

**Table 1 Tab1:** Participant timeline

Timeline	Event
First consultation	Interest in study participation and preliminary eligibility is established at first consultation at the obstetric outpatient clinic (around 18 weeks gestation), and written information is emailed to possible participants.
− 2 weeks	Interview to determine eligibility and participation within two weeks from first consultation.
− 3 weeks	Motivational interviewing (MI)
	Baseline questionnaire
0	Randomization
+ 2 weeks	Start of the intervention (9 weeks)
T1 (1½ months)	1½ months post-randomization: second and intermediate assessment
T2 (3 months)	3 months post-randomization: Third assessment
T3 (6 months)	6 months post-randomization: Fourth assessment
T4 (9 months)	9 months post-randomization: Fifth and final assessment

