### Outcomes

Primary, secondary and exploratory outcomes include validated self-report questionnaires and data from medical records. Questionnaires are collected at the following five time points in both the intervention and waitlist control group: at baseline, prior to randomization (T0), 1½ months post-randomization (T1), 3 months post-randomization (T2), 6 months post-randomization (T3) and 9 months post-randomization (T4). The questionnaire packet is built and managed via REDCap (Research Electronic Data Capture) hosted by Aarhus University. REDCap is a secure web application for building and managing online surveys. In case of non-response, reminders are emailed after one week. Table 2 presents an overview of included questionnaires and time points for assessments.

**Table 2 Tab2:** Overview of self-report questionnaires and time points for assessments

Questionnaire/assessment	Latent variable	T0	T1	T2	T3	T4

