***Primary outcome measure***						
The Who – Well-Being Index	Mental well being	X	X	X	X	X

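### The primary WHO-5 model leaves out the 1½-month score, so women who answer then but never again contribute only their baseline

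*Protocol article*

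**What the plan says.** All places are in the protocol article.

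- **Outcomes.** "Questionnaires are collected at the following five time points in both the intervention and waitlist control group"; the list that follows includes T1 at 1½ months. In Table 2 the row for "The Who – Well-Being Index" is marked in all five columns. The Edinburgh scale and DASS-21 are not marked at T1; both mediators are.
- **Design, Table 1.** T1 is described as "1½ months post-randomization: second and intermediate assessment". Classes start 2 weeks after randomization and run for 9 weeks.
- **Statistical analysis plan, primary model.** The time factor is "time (baseline, 3, 6 and 9 months post-randomization". Scheduled group and person enter as random effects. The quantity to be estimated is defined as follows: "The primary effect estimate is the mean difference in change since baseline between the intervention group and the control group at nine months post-randomization".
- **Statistical analysis plan, population.** The intent-to-treat set is "all randomized participants with completed baseline assessments".
- **Statistical analysis plan, mediation.** "The five measurement points allow to test whether changes in the proposed mediators" are related to changes in outcomes. This is the only analysis said to use all five times.
- **Statistical analysis plan, sensitivity analyses.** "missing outcomes after baseline will be imputed as the model based estimated value when using the observed data, plus a systematic deviation", the deviation being 0.2 SD up or down in one arm at a time. No use of the 1½-month score is stated.

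No reason is given for leaving 1½ months out of the primary model.

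**The concern.** A likelihood-based mixed model is valid when missingness depends only on data that are in the model. Classes run from about week 2 to week 11, so T1, at about 6.5 weeks, is the only WHO-5 score taken while the course is under way. For a woman who answers at T1 and then stops, it is also her only score after baseline. With T1 left out, loss that depends on the T1 score is no longer missing at random for this model, although the information that would make it so has been collected.

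The Sample size section expects 30% not to complete. The arms ask different things of the women (nine classes and home practice against usual care), so arm-specific loss is plausible. The accuracy of the nine-month contrast is what is at stake.

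**Working it through.** **1. The plan's own figure.** Inputs from Sample size: 240 randomized, 168 completing (84 per arm at 1:1), SD 15.6, two-sided alpha 5%.

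SE = 15.6 × √(2/84) = 2.407. Power = Φ(difference/SE − 1.960).
- Difference 7: Φ(2.908 − 1.960) = 82.8% (82.4% with the noncentral t). Stated: 82%.
- Difference 8: Φ(3.324 − 1.960) = 91.4% (91.1% with the t). Stated: 91%.

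Both reproduce. This is a two-group comparison of completers and does not involve T1.

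**2. Assumptions for the rest.** The documents give no within-person correlation, no timing of the 30% loss and no split by arm. The following are therefore assumed: correlation either equal at all visits or decaying with time; 10% or 30% of an arm lost after T1; logit of loss falling by 0.7 or 1.5 per SD of the T1 score.

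**3. Precision.** Generalised-least-squares variance of the nine-month contrast, 120 per arm, 30% monotone loss, without and then with T1:
- Equal correlation 0.5, all loss between T1 and T2: SE 2.085 to 2.050 (1.7% smaller), power for 7 points 91.9% to 92.7%.
- Equal correlation 0.7, same loss: SE 1.719 to 1.675 (2.6% smaller).
- Correlation decaying at 0.4 per 3 months, same loss: SE 2.402 to 2.400 (0.1% smaller).

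Over all settings the gain is 0-3% in SE and at most 0.9 percentage points of power.

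**4. Bias of one arm's nine-month mean, covariance fitted correctly.** Month-9 scores are regressed on the retained earlier scores among women still observed, and the prediction is averaged over all women. Large-sample results in WHO-5 points, correlation 0.5-0.7 (per 3 months where decaying):

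| Correlation | Lost after T1 | T1 left out | T1 used |
|---|---|---|---|
| Equal | 10% | 0.19 to 0.49 | within 0.1 of 0 |
| Equal | 30% | 0.63 to 1.34 | within 0.1 of 0 |
| Decaying | 10% | 0.05 to 0.24 | within 0.1 of 0 |
| Decaying | 30% | 0.27 to 0.73 | within 0.1 of 0 |

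This reaches the treatment contrast only as far as the loss differs between arms; a shift common to both arms cancels.

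**5. The model as written.** A random effect of person, read as a random intercept, implies the same correlation between any two visits. Bias of the contrast under that model, with 30% lost after T1 depending on the T1 score in the MBSR arm only:

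| True correlation | T1 left out | T1 added, random intercept kept |
|---|---|---|
| 0.5 at all visits | +0.7 to +1.3 | about 0 |
| 0.7 × 0.93^months | +0.3 to +0.5 | −0.4 to −0.75 |
| 0.9^months | −0.1 to −0.45 | −0.7 to −1.5 |

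When correlation decays, the random intercept gives T1 too much weight in predicting month 9, so adding T1 alone reverses or enlarges the bias. With T1 and an unstructured covariance together, the bias was within about 0.2 of zero in every case.

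**The case against.** The strongest reply is that the omission looks deliberate and harmless. T1 is labelled intermediate, both mediators are measured then, and the five times are tied to mediation. The secondary scales are not collected at T1, so baseline, 3, 6 and 9 months gives one model form for all outcomes. That explanation is reasonable, and nothing in the article is contradicted. It does not require dropping T1 from the WHO-5 model, however.

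Second, the bias needs several conditions together: loss after T1, driven by the T1 score, and different by arm. This stands. Only total loss is given, and leaving classes is not the same as leaving questionnaires, which are online with emailed reminders.

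Third, the sensitivity analyses already probe shifts of this order: 0.2 × 15.6 × 0.30 = 0.94 points on an arm's mean. This partly stands: the risk is not ignored. But those analyses start from the model's own estimates, with no stated use of T1, and they leave the primary estimate as it is. The bootstrap addresses standard errors, not this bias.

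A reader might also infer more than the text supports:
- *That these women are excluded.* They remain in the intent-to-treat set through their baseline score.
- *That every early dropout loses data.* Women lost before T1 have no such score to discard.
- *That the sample size is wrong.* It reproduces and does not depend on T1.
- *That the nine-month estimate is biased.* The documents do not establish the conditions for this.

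**Conclusion.** The point holds as a modest weakness in a stated analysis choice. The primary outcome is measured at 1½ months in both arms, the primary model does not use it, and the missing-at-random assumption is weaker than it needs to be.

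If loss after 1½ months depends on that score and differs by arm, the possible bias in the nine-month contrast runs from a few tenths of a point to about 1.3 points against a target of 7. The upper end needs about 30% lost in this way in one arm, strong dependence on the score, and equal correlation across visits. Without arm-specific, score-dependent loss, the benefit is a standard error 0-3% smaller. All of these sizes rest on assumed correlations and dropout patterns.

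**What to change.** For WHO-5, in the Statistical analysis plan section:

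1. Set the time levels to baseline, 1½, 3, 6 and 9 months.
2. Replace the person random intercept with an unstructured, or similarly flexible, within-person covariance; keep the random effect of scheduled group.
3. Keep the nine-month difference in change as the primary estimate.
4. Base the imputations in the four sensitivity analyses on this model.

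Steps 1 and 2 belong together, because step 1 alone can make matters worse. If 1½ months is to stay out on purpose, the plan should say why.

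The cost is small. The data are already being collected and participants are not affected. An unstructured covariance over five visits has 15 parameters (5 × 6 / 2), and the WHO-5 model would no longer share its time levels with the Edinburgh scale and DASS-21 models.

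### The primary WHO-5 analysis leaves each arm its own baseline mean and reports a difference in change, which is valid but less precise than a baseline-adjusted analysis of the same nine-month contrast

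*Protocol article*

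**What the plan says.** All of this is in the protocol article. Under Statistical analysis plan, the repeated-measures model has "time (baseline, 3, 6 and 9 months post-randomization" as its time levels, so baseline WHO-5 is part of the response. The fixed effects include "intervention (prenatal MBSR, waitlist control group), interaction between time and intervention" (arm is in fact listed twice, under two names), plus "baseline values of: age, perceived stress and use of psychotropic drugs". On clustering: "The model will include random effects of person and" scheduled group. The target is then named: "The primary effect estimate is the mean difference in change since baseline between the intervention group and the control group at nine months post-randomization". For the rest, "Equivalent models will analyze secondary outcomes, stress, anxiety and depression".

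The section states no common baseline mean across arms, no baseline WHO-5 covariate and no covariate-by-time term. The attachment model in the same section does list baseline wellbeing as a covariate.

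Under Sample size: "The primary outcome is change in mental well-being (WHO-5) from baseline to post-intervention", and "Out of 240 pregnant women, 168 (70%) is expected to complete the study". The SD is 15.6 from the feasibility trial, without saying whether it belongs to the score or to the change. Stated power is 82% for 7 points and 91% for 8.

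**The concern.** With baseline in the response, an arm main effect and an arm-by-time interaction, each arm has a free baseline mean. The nine-month contrast is then a difference in differences that carries the full sampling noise of baseline. Randomization makes the two baseline means equal in expectation, so estimating them separately buys nothing.

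A term for age, baseline stress or psychotropic use that is constant over time shifts every visit by the same amount. It drops out of a within-person change, so the listed adjustment does little for the result it was presumably meant to sharpen.

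At stake are the width of the primary confidence interval and exposure to chance baseline imbalance, in a trial of 240 women that expects to lose 30% of them.

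**Working it through.** **Inputs from the article.** 240 randomized 1:1; 168 completers, so 84 per arm; SD 15.6; two-sided alpha 5%; differences of 7 and 8 points.

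**Assumed, because not given.** The correlation r between baseline and nine-month WHO-5 (0.3 to 0.8), and equal variances at the two times.

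**1. The stated power.** Noncentral t with 166 df. The standard error is 15.6 × √(2/84) = 2.407. For 7 points the noncentrality is 7/2.407 = 2.91 and power is 82.4%; for 8 points power is 91.1%. Both stated figures reproduce.

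**2. What the contrast contains.** Write the mean at time t as α_t + (β + γ_t) × arm + δ′X, with X the baseline covariates. The between-arm difference in change at nine months is γ_9 − γ_0. Neither β nor δ′X remains in it.

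**3. Variance per person, complete data.** With score variance s²:
- change score: 2s²(1 − r)
- adjusted for baseline, or common baseline mean: s²(1 − r²)
- ratio, adjusted to change: (1 + r)/2, so the saving is (1 − r)/2

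| r | saving in variance |
|---|---|
| 0.3 | 35% |
| 0.5 | 25% |
| 0.7 | 15% |
| 0.8 | 10% |

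**4. Power for 7 points, 84 per arm, under both readings of 15.6.**

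If 15.6 is the SD of the change, the adjusted SD is 15.6 × √((1 + r)/2):

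| r | adjusted SD | power, change | power, adjusted |
|---|---|---|---|
| 0.3 | 12.58 | 82% | 95% |
| 0.5 | 13.51 | 82% | 92% |
| 0.7 | 14.38 | 82% | 88% |

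If 15.6 is the SD of the score, the change SD is 15.6 × √(2(1 − r)) and the adjusted SD is 15.6 × √(1 − r²):

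| r | change SD | power, change | adjusted SD | power, adjusted |
|---|---|---|---|---|
| 0.3 | 18.46 | 69% | 14.88 | 86% |
| 0.4 | 17.09 | 75% | 14.30 | 88% |
| 0.5 | 15.60 | 82% | 13.51 | 92% |
| 0.7 | 12.08 | 96% | 11.14 | 98% |

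**5. Simulation of the model as described.** 600 trials of 240 women, four times, random person intercept, r = 0.5, three covariates assumed to explain half the between-person variance, no scheduled-group effect. Entries are empirical standard errors of the nine-month contrast.

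| | complete data | 30% dropout |
|---|---|---|
| planned model, without covariates | 2.03 | 2.28 |
| planned model, with covariates | 2.03 | 2.28 |
| common baseline mean, without covariates | 1.75 | 2.07 |
| common baseline mean, with covariates | 1.63 | 1.99 |

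With complete data, the planned estimate with covariates equals the raw difference in change scores to about 1e-13. With 30% dropout, adding the covariates changes the planned estimate (SD of the shift 0.29 points, largest 1.0) but not its standard error. The constraint alone then lowers the variance by 1 − (2.07/2.28)² = 18%; with covariates as well, by 1 − (1.99/2.28)² = 24%. Across simulations with other settings and 30% dropout, the constraint alone gave up to about 22% at r = 0.5 and about 8–11% at r = 0.7.

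**The case against.** The strongest reply is that nothing here is invalid. The difference in change is unbiased under randomization and keeps its type I error, and the article is consistent: its sample size section defines the outcome as a change and its model estimates one. That stands. This is a matter of efficiency and of chance imbalance.

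Three stronger readings are tempting, and the article does not support them.

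- **That the covariates have no effect on the primary result.** This is exact only for complete data. With the dropout the article expects, the mixed model borrows from earlier visits and the covariates do move the estimate, by up to about 1 point in the simulation. What they fail to add is precision.
- **That the trial is underpowered as planned.** This needs 15.6 to be the SD of the score and r to be below 0.5. If 15.6 is the SD of the change, the planned analysis has the power stated, before any allowance for clustering.
- **That the stress model certainly uses the same score on both sides.** Calling the secondary models equivalent does not say that the covariate list is copied unchanged. Table 2 offers only the DASS-21 as a stress measure, so the overlap is likely if it is copied, but that is an inference. It needs a clarifying sentence.

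It is also fair that the gain could be modest: at high r little is lost, and r is unknown.

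**Conclusion.** The point holds as a recommended improvement, not as an error that invalidates the analysis. The article fixes the response times, fixed effects, covariates, random effects and primary contrast, and together these define a difference in change with a free baseline mean in each arm. Only an explicit common-baseline constraint would remove the concern, and none is stated.

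Under equal variances the planned analysis is less precise for every r below 1. For middling correlations the loss is worth recovering; near r = 0.8 it is small. The range rests on assumed correlations, and the power figures also on which SD 15.6 represents. The conclusion that the listed covariates bring essentially no precision to the primary contrast comes from the algebra with complete data and from simulation under dropout.

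**What to change.** Keep the repeated-measures model and the nine-month between-arm target, and do one of the following:

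- constrain the arms to a common baseline mean: drop the arm main effect, and keep time and arm-by-time at 3, 6 and 9 months only; or
- model 3, 6 and 9 months as outcomes, with baseline WHO-5 by visit as a covariate. The analysis population already requires completed baseline assessments, so this loses no one.

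Optionally let age, baseline stress and psychotropic use interact with visit. List the arm factor once. Treat each secondary outcome in the same way with its own baseline value, and state that the stress model does not carry baseline stress as both response and covariate. State also whether 15.6 is the SD of the score or of the change.

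The cost is small but not nil. Recruitment began in March 2022 and allocation is not blinded, so the change needs a dated, justified amendment made before outcome data by arm are examined. Covariate-by-visit terms add a few parameters to each bootstrap refit. No new data are needed.

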### Study aims

The overall aim of the study is to address the need for a wider array of evidence-based and non-pharmacological options to reduce stress and support resilience in pregnant women with a preconception history of mental disorders or psychosocial vulnerabilities. The intention of mindfulness meditation training in this context is twofold: (1) to improve mental wellbeing and reduce symptoms of stress, anxiety and depression, (2) to engage and strengthen pregnant women´s internal resources for coping more effectively with the challenges and demands of pregnancy and motherhood including building a positive relation to the child. In more detail, the primary aim of the RCT is to estimate the effect of prenatal MBSR as an add-on to usual care on mental wellbeing in psychosocially vulnerable pregnant women when compared to usual care alone. Second, to estimate the effect of prenatal MBSR on perceived stress, symptoms of depression and anxiety. Third to examine if mindfulness and self-compassion mediate an effect of the intervention on outcomes and fourth, to explore the effect on maternal antenatal attachment and childbirth, e.g. gestational age at birth and experience of the birth. To fulfill these aims the MBSR program was adapted to fit a clinical context and named prenatal MBSR [41].

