### Secondary outcome measures

#### Depression Anxiety Stress Scales

The Depression Anxiety Stress Scales (DASS-21) has three subscales designed to discriminate between depression, anxiety and stress in the last week [45]. The DASS excludes somatic items such as sleep disturbance, lack of energy and poor concentration, which may not be valid markers in pregnancy or the postpartum period [46]. Each subscale includes seven items. Response to each item is rated on a four-point Likert scale ranging from ‘never’ to ‘very much/most of the time’. Scores are calculated for each subscale and higher scores point to more symptoms of depression, anxiety or stress. The DASS-21 has shown good psychometric properties [47].

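### As written, the stress model uses baseline stress both as an outcome value and as a covariate, which biases the nine-month stress effect if dropout depends on baseline stress differently in the two arms

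*Protocol article*

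**What the plan says.** All references are to the protocol article. Under Statistical analysis plan, the model for the primary outcome has the terms "time (baseline, 3, 6 and 9 months post-randomization), intervention (prenatal MBSR, waitlist control group), interaction between time and intervention", so the baseline measurement is one of the modelled responses. Its covariates are "baseline values of: age, perceived stress and use of psychotropic drugs", with no interaction with time stated. Woman and course group enter as random effects. The target is the "mean difference in change since baseline between the intervention group and the control group at nine months post-randomization".

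For the secondary outcomes the section says "Equivalent models will analyze secondary outcomes, stress, anxiety and depression" and makes no exception for stress.

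Study aims gives the second aim as "to estimate the effect of prenatal MBSR on perceived stress, symptoms of depression and anxiety". Under Outcomes, Table 2 lists one instrument that yields a stress score, the DASS-21, which "has three subscales designed to discriminate between depression, anxiety and stress in the last week". The list under Participant characteristics contains no other stress measure. Sample size expects 168 of 240 women (70%) to complete.

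**The concern.** In the WHO-5, anxiety and depression models, baseline stress is a different variable from the outcome and nothing is duplicated. In the stress model it is the first response and also a predictor of every response, with one slope. That slope would have to be 1 at baseline, where outcome and covariate are the same number, and equal to the correlation with baseline at each later visit. No single value fits both.

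A likelihood-based mixed model is normally trusted to handle dropout that depends on observed values such as baseline stress. A misfit tied to baseline stress can forfeit that protection. Stress is a named aim, the trial is unblinded, only the MBSR arm carries the course during follow-up, and 30% loss is expected. Dropout that depends on stress in one arm more than the other is therefore plausible, although the protocol does not show it.

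**Working it through.** **Planned figures.** With 84 completers per arm and SD 15.6, the standard error is 15.6 × √(2/84) = 2.41. Power by the noncentral t is 82.4% for 7 points and 91.1% for 8 points, which agrees with the stated 82% and 91%. These figures are for WHO-5; none is given for stress. The 7-point target is 7/15.6 = 0.45 SD, and the simulations below use 0.45 SD as the true reduction in stress.

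**Why one slope cannot fit.** Take a standardised stress score with correlation ρ between any two visits (ρ is not in the protocol; 0.3, 0.5 and 0.7 are assumed). With four complete visits the slope on baseline stress is the average of 1, ρ, ρ and ρ, that is b = (1 + 3ρ)/4:

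- ρ = 0.3: 0.475
- ρ = 0.5: 0.625
- ρ = 0.7: 0.775

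The simulated fits gave 0.47, 0.63 and 0.78. A woman 1 SD above the mean at baseline then has a residual of 1 − b at baseline and an expected residual of ρ − b later. At ρ = 0.5 these are +0.375 and −0.125. The random intercept reads the positive baseline residual as a reason to expect a positive one later, which is the wrong sign.

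**What this does to the contrast.** With complete data the arm-by-visit means do not depend on this, and fits with and without the duplicate covariate agreed to rounding error. With dropout, the missing visits are in effect predicted with an error proportional to baseline stress. If the two arms lose the same kind of women, the errors cancel; if not, they remain. Because the error is linear in baseline stress, its sign follows the direction of the dependence: toward zero when the more stressed women leave the MBSR arm, away from zero when the pattern is mirrored.

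**Bias by simulation.** Random-intercept fits to 100,000 simulated women, about 28–30% lost by nine months, other covariates and course group left out. Entries are bias in SD units; positive is toward zero.

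| Loss mechanism | ρ | Literal model | Baseline as outcome only | Baseline as covariate only |
|---|---|---|---|---|
| Random | 0.3 | 0.019 | 0.019 | 0.016 |
| Random | 0.5 | −0.005 | −0.005 | −0.001 |
| Random | 0.7 | 0.008 | 0.007 | 0.004 |
| On baseline stress, same in both arms | 0.3 | 0.014 | 0.014 | 0.015 |
| On baseline stress, same in both arms | 0.5 | −0.006 | −0.007 | −0.009 |
| On baseline stress, same in both arms | 0.7 | −0.001 | −0.001 | 0.001 |
| On baseline stress, MBSR arm only | 0.3 | 0.052 | −0.001 | −0.007 |
| On baseline stress, MBSR arm only | 0.5 | 0.050 | 0.010 | 0.010 |
| On baseline stress, MBSR arm only | 0.7 | 0.027 | 0.000 | −0.001 |
| On baseline stress, opposite by arm | 0.3 | 0.114 | 0.001 | 0.000 |
| On baseline stress, opposite by arm | 0.5 | 0.084 | −0.002 | 0.000 |
| On baseline stress, opposite by arm | 0.7 | 0.052 | −0.003 | −0.005 |

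In the first two mechanisms the literal model and the model without the duplicate agree to 0.001, so what deviates from zero there is simulation noise. Opposite dependence on the last observed score gave about 0.01 to 0.03 SD in the literal model.

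Other assumed settings moved the range. With 70–71% completing, ρ = 0.35 from baseline to nine months and loss depending on earlier stress differently by arm, the bias was 0.02 to 0.04 SD. With 65–70% completing and ρ from 0.35 to 0.7, it was 0.03 to 0.08 SD for dependence in the MBSR arm only and 0.08 to 0.16 SD for opposite dependence.

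**Scale.** The planned missing-data sensitivity analyses shift imputed values in one arm by 0.2 SD. With 30% missing that moves the contrast by 0.3 × 0.2 = 0.06 SD, so the bias is of the same order as the departures the sponsor chose to examine.

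**Precision, a separate matter.** Standard errors (SD units) from 800 simulated trials of 240 women with 30% random loss:

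| ρ | Literal model | Duplicate covariate dropped | Baseline as covariate only | Excess variance, literal over covariate only |
|---|---|---|---|---|
| 0.3 | 0.1761 | 0.1737 | 0.1506 | (0.1761/0.1506)² − 1 = 37% |
| 0.5 | 0.1510 | 0.1503 | 0.1359 | (0.1510/0.1359)² − 1 = 23% |
| 0.7 | 0.1119 | 0.1118 | 0.1088 | (0.1119/0.1088)² − 1 = 6% |

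Dropping the duplicate alone gains almost nothing. The gain comes from adjusting for baseline in place of a change contrast with a free arm difference at baseline.

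**The case against.** **The literal reading is not forced.** The same section applies an equivalent model to childbirth experience after describing a change-from-baseline model, yet that questionnaire is given only at six months. The authors evidently use the word loosely, and leaving out a covariate that is itself the outcome would be an ordinary adaptation that a fuller plan might record. The covariate's instrument is also not named. This stands as a reason for caution. It does not remove the point, because the text defines the model, extends it to stress and makes no exception, and no second stress measure is listed.

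**The bias is modest and conditional.** At ρ = 0.3 it is 0.052/0.176 = 0.30 of a standard error for one-arm dependence and 0.114/0.176 = 0.65 for opposite dependence. The larger figures need opposite mechanisms in the two arms, which nothing in the protocol establishes. This stands and limits the weight of the point.

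**The bootstrap protects inference.** Resampling women guards the standard error against the misfitted variance. It does not remove bias.

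A reader might also infer two stronger claims. One is that 30% loss, or any stress-related loss, biases the stress effect; the first six rows of the bias table show otherwise. The other is that the duplicate costs precision; it does not, and the precision loss that exists is shared by every outcome analysed with this change contrast, WHO-5 included.

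**Conclusion.** The point holds in limited form. As written, baseline stress is both response and covariate in the stress model, and the single slope makes that model misspecified. The nine-month contrast is unharmed with complete data, random loss, or loss related to baseline stress equally in both arms. With arm-differential, stress-related loss it is biased by roughly 0.02 to 0.08 SD in milder or one-arm cases (0.01 in the mildest) and by about 0.05 to 0.16 SD under opposite dependence. Models that use baseline stress once are not biased in these settings.

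Separately, the change contrast carries about 6% to 40% excess variance over baseline adjustment for correlations from 0.7 down to 0.3 under 30% random loss.

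These sizes rest on assumed correlations and loss mechanisms, and on the perceived-stress covariate being the DASS-21 stress score. The documents do not support extending the point to the primary analysis: baseline stress is not the WHO-5 outcome, so there is no duplication there. Because the remedy is so cheap, the sponsor should make the change.

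**What to change.** State that in the stress model baseline stress is used once, in one of two ways:

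1. Take 3, 6 and 9 months as the outcomes, with baseline stress and its interaction with time as covariate terms.
2. Keep baseline as an outcome, constrain the arm means to be equal at baseline, and drop the perceived-stress covariate.

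Either removes the conditional bias and recovers the precision. Merely deleting the duplicate covariate would remove the bias but leave the standard error practically unchanged.

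The cost is a sentence of model wording and no new data. The one drawback is that the stress model would differ in structure from the models for the other outcomes, unless those are handled the same way.
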